**Figure 1: Study Schema**

[figure not shown]

Prior to delivery a member of the research team or other senior doctor will approach parent(s)/guardian(s) of eligible infants to inform them about the study. Randomisation will occur at delivery. Infants will then be monitored for the duration of their hospitalisation, looking at a large number of secondary outcomes. Subjects' participation will be from time of birth until discharge from hospital.

Infants in the treatment arm will receive oropharyngeal surfactant immediately after birth and then be stabilised on CPAP. Infants in the control arm will be stabilised on CPAP immediately after delivery. Infants will then receive standard care, regardless of their group assignment. Enrolled infants will be intubated for persistent apnoea and/or bradycardia in the DR, or for respiratory failure in the NICU as specified in the protocol. Should infants in either group meet the criteria for respiratory failure following initial randomisation, they will be intubated and surfactant will be administered for treatment of RDS, irrespective of group assignment (i.e. whether or not they have previously received oropharyngeal surfactant). Further surfactant administration and all other aspects of neonatal intensive care will be at the discretion of the treating physicians.

All babies in both groups will be closely watched to see if they need extra treatment for their RDS at any stage, including surfactant given endotracheally. The babies will be treated equally and given whatever treatment is necessary, whether or not they have already been given surfactant into the oropharynx.

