#### **11.4 Definition of end-of-trial**

The end of the trial will be when all infants have been recruited and the last baby has been discharged from hospital, in order to ensure all secondary outcomes have been recorded. On occasion, surviving premature infants have a surgical intervention (e.g. tracheostomy, bowel resection) that renders them dependent on technology (e.g. positive pressure respiratory support, parenteral nutrition). These infants may remain as hospital in-patients for months or years beyond their expected date of delivery (EDD). It is not possible to identify these infants at enrolment. If one such infant is enrolled in the study, waiting to collect their discharge-based secondary outcome data (date of discharge, duration of hospitalisation, receipt of home oxygen) would indefinitely defer the analysis of the primary outcome and other secondary outcome data for all participants. After enrolment is complete, it will be determined whether any infant who remains in hospital one month beyond their EDD remains in receipt of supplemental oxygen and their primary and other secondary outcome data (up to Section I of the Case Record Form) will be locked for analysis at that point. These infants will be followed to ascertain their date of discharge and duration of hospitalisation (Section J). The participation of infants who remain as in-patients 6 months after their EDD will be censored, and their duration of hospitalisation will be recorded at that point.

The Sponsors and/or the trial steering committee, however, have the right at any time to terminate the study for clinical or administrative reasons.

The end of the study will be reported to the REC and Regulatory Authority within 90 days, or 15 days if the study is terminated prematurely. The investigators will inform subjects and ensure that the appropriate follow-up is arranged for all involved.

A summary report of the study will be provided to the REC and Regulatory Authority within 1 year of the end of the study and within 6 months for paediatric studies. This is a legal requirement.

The end-of-trial is the date of the last visit/telephone follow-up/home visit of the last subject. The end of study visit forms should include:

- assessment of endpoints/outcome measures

- assessments of safety including adverse event collection
- assessment of compliance with study treatment(s)
- recording of concomitant medications

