#### 14.5.2 Secondary efficacy endpoints

Each categorical secondary endpoint will be analysed with the following approach.

- Descriptive statistics will be calculated to compare the rate of occurrence of the endpoint across treatment groups (frequency, percentage). Ratios of relative risk will be presented with 95% confidence intervals.
- A superiority hypothesis test (two-sided, two-proportion Z test) will be carried out to investigate whether the rate of occurrence of the endpoint differs between intervention and standard-of-care.

For the important secondary endpoint of death before hospital discharge, regression analysis will be employed to determine sensitivity of the estimated intervention effect to potentially relevant covariates; including centre, gestational age, birth weight, gender, mode of delivery (vaginal versus caesarean birth) and antenatal corticosteroid treatment.

Each quantitative secondary endpoint (e.g. duration of mechanical ventilation, duration of hospitalisation), will be analysed using the following approach.

- Descriptive statistics will be calculated to compare the endpoint across treatment groups (mean, median, standard deviation, IQR, min, max). The difference in means (or medians where relevant) between treatment groups will be presented with a 95% confidence interval.
- A superiority hypothesis test (two-sided independent sample t-test) will be carried out to test for a difference in means between control and intervention. Alternatively, if t-test assumptions are not valid, a Mann-Whitney U test will be carried out to test for a difference in the endpoint between control and intervention.

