For the time-to-event endpoint death before hospital discharge, Kaplan-Meier curves will be constructed to visualize the pattern of mortality over the study period, with median survival time reported with 95% confidence intervals. Cox proportional hazards regression will be used to quantify the hazard ratio for those treated with oropharyngeal surfactant vs standard-of-care. A Cox proportional hazards regression model will also be fitted to determine sensitivity of the estimated intervention effect to potentially relevant covariates; including centre, gestational age, birth weight, gender, mode of delivery (vaginal versus caesarean birth) and antenatal corticosteroid treatment.

Each numeric secondary endpoint (e.g. duration of mechanical ventilation, duration of hospitalisation), will be analysed using the following approach.

- Descriptive statistics will be calculated to compare the endpoint across treatment groups. This will include the frequency of missing data per treatment arm, minimum and maximum values, mean and standard deviation for symmetrically distributed variables and median and interquartile range for asymmetrically distributed variables. The difference in means (or medians where relevant) between treatment groups will be presented with a 95% confidence interval. Confidence intervals for the difference in means will use a Normal approximation while confidence intervals for the difference in medians will be calculated by bootstrap resampling.
- A superiority hypothesis test (two-sided independent sample t-test) will be carried out to test for a difference in means between control and intervention. Alternatively, if t-test assumptions are not valid, a Mann-Whitney U test will be carried out to test for a difference in the the endpoint between control and intervention.

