## 6. Changes from the protocol

The SAP is consistent with the main features of the statistical methods described in the protocol.

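### SAP 5.1.1 plans a median survival time, Kaplan-Meier curves and Cox regression for death before discharge without saying how infants discharged alive are handled; the median is unusable and the tail of the curve may overstate mortality

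*Combined protocol and SAP*

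**What the plan says.** SAP 5.1.1, under the analysis of secondary endpoints, treats death as a time-to-event outcome: "Kaplan-Meier curves will be constructed to visualize the pattern of mortality over the study period, with median survival time reported with 95% confidence intervals". It continues: "Cox proportional hazards regression will be used to quantify the hazard ratio for those treated with oropharyngeal surfactant vs standard-of-care". A second, covariate-adjusted Cox model follows.

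Follow-up is described in protocol 11.1: "Subjects' participation will be from time of birth until discharge from hospital". The only censoring rule in either document is in protocol 11.4 and concerns long-stay infants: "The participation of infants who remain as in-patients 6 months after their EDD will be censored". Neither document says what happens in the Kaplan-Meier or Cox analysis to an infant who goes home alive. The competing-risks model in SAP 5.1.2 is for the primary endpoint only.

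For categorical secondary endpoints, protocol 14.5.2 gives descriptive rates, "Ratios of relative risk will be presented with 95% confidence intervals", and a two-sided two-proportion Z test. For death it adds a regression analysis of unspecified type. SAP 5.1.1 also gives categorical secondary endpoints the same treatment as the primary endpoint, and SAP 1.3 lists death as a factor variable. SAP section 6 says: "The SAP is consistent with the main features of the statistical methods described in the protocol".

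**The concern.** Discharge alive is not ordinary censoring. Infants go home because they are well, so those still in hospital at a late date are the sickest. Kaplan-Meier assumes that a censored infant has the same future risk as one still under observation. If discharge is coded as censoring, each late death is divided by a small, selected risk set and the curve drops too far. A reader could then see plotted mortality well above the share of infants who died. A median survival time raises a separate difficulty, because it has no meaning unless about half the infants die.

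The endpoint carries weight. The documents call death before discharge the important secondary outcome, and it is one of the two outcomes in the interim stopping rule. The SAP also leaves unclear whether the relative risk and Z test still apply to death once it is labelled time-to-event.

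**Working it through.** **Inputs from the documents.** The planned total is 250, allocated 1:1. It reproduces. For 46% versus 28%, two-sided 5%, 80% power, pooled variance, the size per arm is [1.96·√(2·0.37·0.63) + 0.842·√(0.46·0.54 + 0.28·0.72)]² / 0.18² ≈ 111.8, so 112 per arm and 224 in all. Then 224/0.9 = 248.9, so 249, against the stated 250. The documents give no figure for the mortality analysis. Their only death rate is 10%, described as before 120 hours. Mortality to discharge, timing of deaths and timing of discharge are all absent and are assumed below.

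**Step 1: the median with survivors kept event-free.** The curve reaches 50% only if at least 125 of 250 infants die, so the probability is P(X ≥ 125) with X ~ Binomial(250, p):

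| Mortality p | Probability that a median exists |
|---|---|
| 10% | 2 × 10⁻⁵⁷ |
| 20% | 4 × 10⁻²⁶ |
| 30% | 3 × 10⁻¹¹ |
| 40% | 9 × 10⁻⁴ |

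**Step 2: why discharge censoring inflates the tail.** A death with r infants at risk multiplies the survival estimate S by (1 − 1/r), a drop of S/r. Take 15% mortality with 10% of deaths late. Early deaths are 13.5% of infants, so S = 0.865 before the late ones. One more death is 1/250 = 0.4 percentage points of the crude proportion. If, for illustration, 25 infants remain in hospital, the curve drops by 0.865/25 = 3.5 points.

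**Step 3: size of the effect on the curve.** Simulations censored survivors at discharge, with true mortality 15%. The day-120 row assumes 125 infants per arm, discharge at mean day 90 (SD 20), and 10-20% of deaths late. The rows for days 100, 150 and 240 assume 250 infants, discharge around 38.5 weeks postmenstrual age (SD 2 weeks) with a 6% long-stay tail, and 5-20% of deaths late.

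| Late deaths fall between | Kaplan-Meier mortality at end of curve |
|---|---|
| none after day 60 | 15% |
| day 60 and day 100 | 16-19% |
| day 60 and day 120 | about 19-22% |
| day 60 and day 150 | 23-43% |
| day 60 and day 240 | 40-71% |

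Up to day 60, before most discharges, the curve equals the crude proportion. With survivors kept event-free to a common horizon, the curve ends at the crude 15% in every scenario. Cumulative incidence with discharge as a competing event gives the same result.

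**Step 4: a median under discharge censoring.** It appears in no runs with late deaths to day 100 and in at most 1.3% with late deaths to day 120. Across mortality of 10-30%, it appears in 0.6-94% of runs with late deaths to day 150 and in 17-99.8% to day 240. Since far fewer than half the infants die, each such median is an artefact.

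**Step 5: the hazard ratio.** With no treatment effect, discharge censoring gave hazard ratios of 0.99-1.04, against 0.97-1.03 with survivors kept at risk. With a true odds ratio of 0.6 and a stay two weeks shorter on treatment, the worst case was 0.66 against 0.62, a ratio of about 1.06. The SD of the log hazard ratio was about 0.39, so the shift is ln(1.06)/0.39 ≈ 0.15 SD. In a separate set with equal mortality, a stay shortened by 10 or 20 days gave 1.07 or 1.16. With about 0.15 × 250 = 37.5 deaths, SE(log HR) ≈ 2/√37.5 = 0.33, so these shifts are about 0.2 and 0.45 SE.

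**The case against.** The strongest reply is that the SAP never says survivors are censored at discharge. For an outcome defined as death before discharge, an infant who has gone home can be carried forward as event-free, and the curve then ends at the true death proportion. This stands: the bias is conditional, and the established defect is an unstated rule. It does not rescue the median, which fails under either coding.

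A reader might infer three stronger things that the documents do not support.

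- That a median can never be computed. Under discharge censoring one can appear (step 4); it is simply not interpretable.
- That the hazard ratio is seriously biased. Cox regression with discharge as censoring estimates a cause-specific hazard ratio for death in hospital, which is a recognised quantity. Its dependence on length of stay is small against sampling error (step 5).
- That the SAP dropped the protocol's binary analysis or contradicts the protocol. The categorical rule in SAP 5.1.1 may still cover death, SAP 5.4 reports deaths by arm, the protocol's unspecified regression could be a Cox model, and SAP section 6 claims agreement only on main features.

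Nor do the documents say that the interim look at death would use the Cox model. They set p < 0.001 and name no test for it.

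**Conclusion.** The point holds, at minor to moderate severity. The median survival time is unsuitable whichever way survivors are coded: undefined at any plausible mortality if they stay event-free, spurious if they are censored and one appears. The SAP also lacks a rule for infants discharged alive. Under the natural default, the tail of the Kaplan-Meier curve overstates mortality whenever deaths occur after discharges begin: about 19-22% for a true 15% in the day-120 scenario, more if deaths come later, and nothing without late deaths. These sizes rest on assumed mortality, death times and discharge times, none of which the documents give. The Cox estimate is usable if it is described as cause-specific, and is not materially distorted at 250 infants. The place of the relative risk and Z test in the analysis of death is ambiguous rather than shown to be lost.

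**What to change.** In SAP 5.1.1:

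1. Delete the median survival time.
2. State how infants discharged alive are handled. Either plot the cumulative incidence of in-hospital death with discharge alive as a competing event, or keep discharged infants event-free to a common horizon in both the curves and the Cox model. If a Cox model with discharge censoring is retained, label its result a cause-specific hazard ratio.
3. Confirm that the relative risk with its 95% confidence interval and the two-proportion Z test, as in protocol 14.5.2 and the SAP's own categorical rule, are the main analysis of death, with the time-to-event results supportive.

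In SAP section 6, record the time-to-event analysis of death as an addition to the protocol.

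The cost is a few sentences of SAP text. Follow-up already runs to death or discharge, so no new follow-up is required.

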### 14.2 Determination of sample size subjects

In randomised studies, the rate of mechanical ventilation in the days after birth among preterm infants treated with CPAP alone has varied from 46– 60%. (2, 11, 19-21) Minimally invasive surfactant techniques were shown to reduce the rate of mechanical ventilation to from 46% to 28% in a cohort of infants with a gestational age between 26 and 28 weeks. (21)

Sample size for this study was calculated in G\*power, using a two-sided, two-proportion Z test. To detect a difference in the rate of endotracheal intubation for respiratory failure of 18% between treatment arms (assuming a rate of 46% in the control group and 28% in the intervention arm) with 80% power and a 5% significance level, a sample size of 224 infants would be required. To compensate for a death rate of 10% (estimated from local data, The National Maternity Hospital, Neonatal Clinical Report for 2015) before the primary outcome can be determined (i.e. at 120 hours), we will need to recruit a total of **250** infants to this study.

The National Maternity Hospital is a stand-alone university maternity hospital with a tertiary NICU to which > 150 infants < 1500g are admitted annually. We have a track record of initiating, conducting, completing, presenting and publishing investigator-led randomised controlled trials, including trials that compared delivery room interventions, (12-14) trials that had respiratory failure in the NICU as the primary outcome (15) and trials that compared investigational medicinal products (16) in preterm infants. Though the enrolment rates to our studies amongst eligible infants are consistently excellent (> 80%), we believe it will be necessary to enrol infants at multiple sites in order to enrol our planned target sample of 250 infants in a timely fashion. We have a track record enlisting the help of collaborators

nationally(16)andinternationally(14, 17)to perform our studies. We believe that with their help, we can enrol these infants in 2–3 years.

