#### Secondary endpoints analysis

Mortality is an intercurrent event that could potentially occur before observation of many of the secondary endpoints in this trial in addition to the primary endpoint. Most secondary outcomes will involve evaluation of the intervention effect to be expected in infants while alive. Analysis of secondary endpoints will be performed on the intention-to-treat set of all randomised infants. The exceptions to this are

- Number of attempts taken to successfully intubate in the delivery room – will only be assessed for those who need to be intubated in the delivery room (intubation in the delivery room is indicated by variable **dr\_infant\_intub.factor**)
- Rectal temperature on admission to NICU as well as NICU intubation will only be evaluated for infants who are admitted to NICU alive (identified by derived variable **nicu\_admission**)

|         |                                           |              |               |
|---------|-------------------------------------------|--------------|---------------|
| UCD CRC | SAP for the POPART trial                  |              |               |
| UCD CRC | Template: Statistical Analysis Plan (SAP) | Version: 1.0 |               |
|         |                                           |              | Page 13 of 19 |

- Bronchopulmonary dysplasia (BPD) – supplemental O2 at 28 days of life - will only be evaluated for infants who are alive at 28 days of life (infants alive at 28 days to be determined by the variable **bpd\_d28.factor** )
- Chronic lung disease of prematurity (CLD), the need for supplemental O2 at 36 weeks corrected gestational age (CGA) determined by physiological oxygen reduction test - will only be evaluated for infants who are alive at 36 weeks CGA (determined by the variable **cld\_36wks.factor** )
- Duration of hospitalisation will be summarized and analyzed both for infants who survive to hospital discharge and for the whole sample. A similar approach will be used for days of mechanical ventilation and days of respiratory support.

Each categorical secondary endpoint will be analysed using the same approach as the main analysis of the primary endpoint.

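### For ventilation days, the fallback Mann-Whitney test is paired with a bootstrapped difference in medians, which does not measure what that test detects

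*Combined protocol and SAP*

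**What the plan says.** SAP section 5.1.1 (Secondary endpoints analysis) sets one rule for every numeric secondary endpoint and names duration of mechanical ventilation as its first example. The rule has three parts.

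- **Effect estimate.** A difference in means or, where relevant, in medians, with a 95% confidence interval. For medians, "confidence intervals for the difference in medians will be calculated by bootstrap resampling".
- **Default test.** A two-sided t-test for a difference in means.
- **Fallback test.** "Alternatively, if t-test assumptions are not valid, a Mann-Whitney U test will be carried out to test for a difference" in the endpoint.

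Protocol 14.5.2 has the same rule without the bootstrap: "The difference in means (or medians where relevant) between treatment groups will be presented with a 95% confidence interval". The protocol synopsis lists only t-tests for continuous outcomes.

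The same SAP section analyses secondary endpoints on all randomised infants, with listed exceptions. Duration of hospitalisation is analysed both in survivors to discharge and in the whole sample, and "A similar approach will be used for days of mechanical ventilation and days of respiratory support". Nothing restricts ventilation days to infants who were ventilated, so an infant never ventilated would enter with 0 days.

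Neither document names the quantity that Mann-Whitney addresses, gives an effect measure to go with it, or says how to read a p-value and an interval that disagree. The SAP's estimand section covers only the primary endpoint.

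**The concern.** Three targets are in play: the t-test compares means, the bootstrap interval estimates a difference in medians, and Mann-Whitney responds to the chance that an infant in one arm has fewer days than an infant in the other, ties counting half. When at least half of each arm has 0 days, both medians are 0 and their difference stays at 0 over a wide range of treatment effects. Mann-Whitney is then driven mainly by the share ventilated and can be clearly significant.

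The report could therefore show p<0.05 for ventilation days beside a median difference of 0 and an interval containing 0, with no rule for reading the two together. The p-value could also be worded as fewer ventilator days on average, which the test does not establish. The protocol's benefit-risk section lists reduced costs and adverse effects of ventilation as potential benefits, so this endpoint will be read closely.

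**Working it through.** **Inputs from the documents.** Protocol 14.2 gives the planning rates, "assuming a rate of 46% in the control group and 28% in the intervention arm", for intubation for respiratory failure within 120 hours. It also says that the rate of mechanical ventilation "among preterm infants treated with CPAP alone has varied from 46– 60"%. Planned enrolment is 250, randomised 1:1, so 125 per arm. The SAP's significance level is 0.05.

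**The plan's own figure.** The protocol states "with 80% power and a 5% significance level, a sample size of 224 infants would be required", "using a two-sided, two-proportion Z test". With pooled variance and no continuity correction, the mean rate is (0.46 + 0.28)/2 = 0.37, and

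n = [1.96·√(2·0.37·0.63) + 0.84·√(0.46·0.54 + 0.28·0.72)]² / 0.18² ≈ 111.8,

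so 112 per arm, or 224. Then 224/0.90 = 249, against the stated 250. This reproduces. The documents give no figure for ventilation days.

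**Assumptions not in the documents.** The 120-hour rates stand in for the share ever ventilated. Days are 0 if never ventilated, otherwise log-normal in whole days, with control mean 8 or 10 and log-SD 1 (0.8 to 1.3 tried). The bootstrap is a percentile interval with 400 or 1,000 resamples. Simulations used 1,000 to 4,000 trials per scenario, with bootstrap intervals computed for only 300 of the trials in some runs.

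**Step 1: medians.** At 46% and 28%, 54% and 72% of the arms are zeros. Both population medians are 0.

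**Step 2: what Mann-Whitney measures.** With equal durations among ventilated infants, the probability that a surfactant infant has fewer days than a control, plus half the ties, is

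0.46·0.72 + 0.5·0.46·0.28 + 0.5·0.54·0.72 = 0.331 + 0.064 + 0.194 = 0.59.

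No effect would be 0.50.

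**Step 3: test and interval, equal durations if ventilated, 125 per arm.** At 46/28, Mann-Whitney gives p<0.05 in about 82% of trials (80% to 82% across runs), and the bootstrap interval excludes 0 in 0.3% or fewer. As the share ventilated rises, with the 18-point difference kept:

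| Ventilated, control/surfactant | p<0.05 and median difference exactly 0 | p<0.05 and interval includes 0 |
|---|---|---|
| 46/28 | about 63% | about 80% |
| 50/32 | 32% to 36% | about 75% |
| 55/37 | about 4% | about 59% |
| 60/42 | about 0% | about 30% |
| 70/52 | about 0% | about 36% |

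**Step 4: a single data set.** Take 125 per arm, with 58 and 35 ventilated and equal durations. The medians are 0 and 0, and Mann-Whitney p = 0.004. If ventilated surfactant infants stay on longer, so that mean days are 4.74 v 4.54 for control, Mann-Whitney still favours surfactant (p = 0.023) while the t-test gives p = 0.89.

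**Step 5: when can mean days be equal or higher?** Suppose surfactant only spares infants ventilation, and all 18 points spared are those with the shortest durations (control mean 8 days, log-SD 1). The remaining 28% then average 11.8 days. Mean days per infant are 0.28·11.8 = 3.3 v 0.46·8 = 3.68, still lower under surfactant (3.16 to 3.47 for log-SD 0.8 to 1.3). Equal means need 3.68/0.28 = 13.1 days among those still ventilated, which is 13.1/11.8 = 1.11 times as long. At 13.1 days, Mann-Whitney favours surfactant in about 63% of trials. At 16 days, where mean days are higher (0.28·16 = 4.48 v 3.68), it does so in about 55%.

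**The case against.** - **The fallback is conditional.** The default is a t-test with a mean difference, and these agree. This stands, but zero-heavy, skewed days are where the fallback is most likely to be invoked.
- **46% and 28% belong to another endpoint.** They are 120-hour intubation rates, the 46%-to-28% reduction comes from a cohort of 26 to 28 weeks, and this trial also enrols infants below 26 weeks. Ventilation days run to discharge. This stands: the exact-zero result depends on the share ventilated and is nearly gone by 55/37. The disagreement between p-value and interval outlasts it.
- **Other results give context.** Ventilation yes/no is tested separately, and Protocol 14.5.2 lists both mean and median by group. This holds in part. The SAP narrows the description to median and interquartile range for asymmetric variables, so mean days might not be shown.
- **Rank methods are a deliberate choice.** Protocol 14.9 allows them when outliers harm the analysis, and a mean comparison has less power here (about 42% v 82% at 46/28 with equal durations). This stands, and is why Mann-Whitney should stay available.

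A reader might go further and infer an inflated type I error, because Mann-Whitney rejects in about 63% of trials when mean days are equal. The documents do not support that. They tie the difference in means to the t-test only. In that scenario the distributions truly differ, so rejection is correct for Mann-Whitney's own null. Nor does sparing the mildest infants raise mean days; step 5 shows that they fall. Equal or higher means require surfactant to lengthen ventilation in infants still ventilated, and nothing in the documents suggests that it does.

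**Conclusion.** The concern holds as a mismatch between test and effect estimate in the fallback branch, for numeric endpoints with a large share of zeros. At 46/28 the median-difference interval carries almost no information: it excludes 0 in under 1% of trials, while the test is significant in about 82%. At 55/37 to 70/52, the p-value and interval still disagree in roughly 30% to 59% of trials. That Mann-Whitney could favour surfactant with equal or higher mean days is a caution about wording, conditional on longer ventilation in those still ventilated.

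The sizes rest on assumed log-normal durations, the assumed share ventilated and use of the fallback. The mismatch itself follows from the SAP's text. Only ventilation days were calculated; doses of post-intervention surfactant may share the problem if many infants receive none. Severity is minor, and the primary analysis and sample size are untouched.

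**What to change.** In SAP section 5.1.1, for days of mechanical ventilation and any other numeric endpoint with a large share of zeros:

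1. Drop the bootstrapped difference in medians as the effect estimate. Keep medians and interquartile ranges as description.
2. When Mann-Whitney is used, report the probability that a surfactant infant has fewer days than a control, plus half the ties, with a 95% confidence interval. Describe the result in those terms.
3. Show the difference in mean days per infant with a Welch 95% confidence interval beside it. Do not word a Mann-Whitney result as fewer mean ventilator days.
4. Present these next to the existing yes/no mechanical ventilation endpoint.

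The cost is SAP wording, a few lines of code and slightly more reporting, with no new data. The probability measure is less familiar to clinicians and will need a sentence of explanation.
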